## Abstract

**Background:**

Medication regimens for asthma are particularly vulnerable to adherence problems because of the requirement for long-term use and periods of symptom remission experienced by patients. Pharmacists are suited to impact medication adherence given their training, skills, and frequent contact with patients. The Empowering pharmacists in asthma management through interactive SMS (EmPhAsIS) trial involves an intervention leveraging mobile health (mHealth) technology to support community pharmacy practice with the hypothesis of improved medication adherence in asthma.

**Methods/Design:**

This study is a pragmatic pharmacy-based, cluster, randomized controlled trial with 12 months of intervention delivery and follow-up. Pharmacies (the clusters) will be randomized at a 1:1 ratio to provide intervention or usual care. The EmPhAsIS intervention consists of patient asthma education, short message service (SMS)-based monthly assessment of adherence, and follow-up of non-adherent individuals by community pharmacists. There are no inclusion or exclusion criteria for pharmacies. Patients are eligible if they: are 14 years of age or older, fill a prescription for inhaled corticosteroid (either monotherapy or in a combination inhaler with long-acting beta-agonists), have been diagnosed with asthma, possess a mobile phone with SMS capabilities, and have no communication difficulties such as inability to communicate in English, or significant impairment in vision, hearing, or speech. The primary outcome is adherence to inhaled corticosteroids ascertained by the medication possession ratio, the ratio of the days of medication supplied to days in a given time interval. This study will also evaluate secondary outcomes including: asthma control, asthma-related quality of life, asthma-related hospital admissions, and use of reliever medications during the follow-up period. A nested economic evaluation using a probabilistic decision-analytic model will be used to perform a cost-effectiveness analysis from the societal perspective of the intervention compared with usual care over a 10-year time horizon.

**Discussion:**

Considering the prevalence of asthma, the extent of the non-adherence problem in this disease, and the availability of effective treatments, there is a tremendous potential to reduce the burden of asthma through improving adherence. This is the first study of an intervention based on mobile communication technology involving community pharmacists in asthma management.

**Trial registration:**

ClinicalTrials.gov identifier: NCT02170883; date of registration: 19 June 2014.

## Background

Asthma is a chronic inflammatory disease of the airways which is characterized by recurrent, but reversible, episodes of shortness of breath, chest tightness, coughing, and wheezing [1]. The global prevalence of asthma is estimated at 300 million [2, 3] and the condition affects individuals of all ages [4]. In 2010, more than 2.4 million Canadians aged 12 years or older reported that they have been diagnosed as having asthma [5]. The ultimate goal of asthma management is to bring the disease under clinical control [6]. Compared to controlled asthma, uncontrolled asthma is associated with increased medical costs, reduced quality of life, and loss of productivity [7].

Pharmacotherapy remains the cornerstone of asthma management. All modern guidelines recommend daily use of controller medications regardless of the level of asthma impairment (with the exception of very mild and intermittent asthma) [6, 8]. Currently, inhaled corticosteroids (ICS) are widely accepted as the primary controller therapy for asthma [6]. Yet despite recommendations, there is a disappointingly low level of adherence to asthma controller therapies [9]. The average rate of adherence to inhaled corticosteroids for asthma is reported to be between 22 and 63% [10–16]. Medication regimens for asthma are particularly vulnerable to adherence problems because of the requirement for long-term use and the long periods of symptom remission experienced by patients [17]. The relationship between adherence to controller therapies and short- and long-term adverse asthma-related outcomes is well established [18, 19]. Landmark studies in the 1990s showed that regular treatment with ICS is associated with up to an 80% reduction in the risk of death, as well as severe asthma exacerbations requiring hospitalization [20–23].

Pharmacists are ideally suited to impact medication adherence given their training, skills, and frequent contact with patients; up to eight times more often than doctors [24]. A few studies have evaluated community-pharmacist-based interventions in the management of asthma. A Spanish cluster randomized controlled trial (RCT), in which patients in the intervention group scheduled three to six visits to their pharmacist over six months of follow-up, reported that adherence was improved by 40.3% in the intervention group compared with the control group [25]. Similarly, an Australian cluster RCT with 50 pharmacies (396 patients), involving an ongoing cycle of assessment, goal setting, monitoring, and review by pharmacists, showed that compared with usual care, the intervention resulted in improved adherence to controller medication (odds ratio for adherence: 1.89) [26]. A cluster RCT of community pharmacists in British Columbia (BC) also showed promising results of an ‘enhanced care protocol’, with pharmacists responsible for assessing a patient’s readiness to change, tailoring asthma education to that readiness, monitoring compliance, and collaborating with physicians to achieve asthma prescribing guidelines [27].

Mobile phones are globally the most pervasive and accessible form of two-way communication technology [28]. The use of mobile phones in public health practice (mobile health, mHealth) [29] offers opportunities to enhance patient care and impact medication adherence across many diseases. Previous studies have considered text messages to be a behavior change communication modality [30]; a process of any intervention with individuals to develop communication strategies to promote positive behaviors [31]. In a multisite randomized clinical trial of HIV-infected adults initiating antiretroviral therapy (ART) in three clinics in Kenya, patients were randomized at a 1:1 ratio to receive weekly short message service (SMS) intervention coupled with clinic nurse follow-up, or standard care. The primary outcome (adherence to ART) was reported in 168 of 273 patients receiving the SMS intervention compared with 132 of 265 in the control group (relative risk (RR) for non-adherence: 0.81; 95% CI: 0.69 to 0.94; *P* = 0.006) [32].

To overcome the epidemic of low adherence, our healthcare system requires innovative models of care that fully harness the knowledge, skills, availability, and enthusiasm of healthcare providers, and facilitate communication across the chain of healthcare delivery [33]. In a critical review of the literature on adherence interventions in asthma, Bender *et al*. concluded that research is encouraged into innovative interventions that are brief, easily implemented, and can be tailored to individual patients and diverse clinical settings [33]. Previous studies have evaluated communication technologies in asthma care [34, 35], but none of these studies have involved pharmacists. On the other hand, pharmacist-based studies on improving the management of asthma have hitherto used interventions whose real-world feasibility and cost-effectiveness have not been evaluated. Altogether, we perceive a role for mHealth to support community pharmacy practice and provide a means for an accessible and cost-effective method of communication between asthma patients, with the ultimate goal of facilitating patient engagement in their disease management, thereby improving adherence and outcomes [35].

## Methods/Design

### Study design

This trial, known as ‘Empowering pharmacists in asthma management through interactive SMS’ (EmPhAsIS), will be implemented from 2015 to 2018 in BC, Canada. It is a pragmatic, cluster RCT trial of a community-pharmacist-initiated, mHealth-supported, adherence intervention (EmPhAsIS intervention) for asthma, with 12 months of participant (pharmacies and patients) recruitment and 12 months of follow-up over which the intervention will also be delivered. Community pharmacies in the province of BC define the clusters based on three reasons. First, patient-level randomization would require each study pharmacist to provide either the intervention or usual care to different patients of the same pharmacy and can lead to contamination. Second, pharmacist-level randomization would require the pharmacist to be both the participant recruiters and randomization units which could lead to selection bias concerns (for example, pharmacists randomized to the intervention group preferentially recruiting patients whom they know are at higher risk of medication non-adherence). Third, given that most pharmacists in community pharmacies are scheduled on a shift-work basis and provide overlapping care to all patients of the pharmacy, the risk of contamination cannot be practically controlled in this environment. To eliminate such randomization problems, it was therefore pragmatically decided to randomize clusters at an organizational level and make these services available on a per pharmacy basis. This trial has been approved by the University of British Columbia Clinical Research Ethics Board (approval number: H14-01451).

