### Participants

#### Pharmacies

Pharmacies will be recruited from an existing database of community pharmacies we have partnered with, of which pharmacists have indicated interest in collaborating with us. Pharmacies (the clusters) will be randomized in a 1:1 ratio to intervention or usual care. All recruited pharmacies will receive pamphlets that will describe the study protocol and the Global Initiative for Asthma (GINA)’s Pocket Guide for Asthma [36]. All pharmacists will attend an online workshop (webinar) during which they will be trained on the study protocol and provided education on asthma and medication adherence as part of the study. Pharmacists will also attend separate webinars (intervention webinar and usual care webinar) and will receive written study manuals specific to whether they have been assigned to the EmPhAsIS intervention or usual care group. There are no inclusion or exclusion criteria for pharmacies.

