### Randomization

Assignment of pharmacies to provide the EmPhAsIS intervention or usual care will be done in a 1:1 ratio with randomly permuted blocks in sizes of four and six. A computer-generated list will be used to ensure balance in the distribution of intervention and usual care groups at any point in the trial while minimizing the risk that research staff may be able to predict group assignment. Clusters will be allocated to intervention or usual care group by one designated research staff member using the computer-generated list. It will not be possible for participating pharmacies to be blinded to which group they are assigned. However, while the trial will be managed by a coordinator who will also be unblinded, team members responsible for data collection (an interviewer who will collect patient-reported data at 0, 6, and 12 months) and analyses (statistical analyst) will be blinded to group allocation.

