### Study groups

#### Intervention (EmPhAsIS) group

Patients attending pharmacies assigned to the intervention group will receive the EmPhAsIS intervention which consists of three main pillars: a) patient education, b) SMS-based monthly assessment of adherence to controller therapies, and c) follow-up of non-adherent individuals by community pharmacists.Patient education: the education component will involve the pharmacist discussing patients’ individual treatments, information on the chronic, episodic nature of asthma and the importance of continuous controller therapy, with emphasis on medication adherence.SMS-based monthly assessment of adherence to controller therapies: The principal component of the intervention is monthly text messages, delivered over the 12 month follow-up period, by which patients are asked to provide their level of agreement with the statement ‘I follow my asthma medication plan’. Responses range on a Likert scale (1: Agreeing completely, 2: Agreeing mostly, 3: Agreeing somewhat, 4: Disagreeing somewhat, 5: Disagreeing mostly, and 6: Disagreeing completely). Individuals will be asked to respond by typing back a number (between one and six) corresponding to the response items. This question and the set of responses are the first item in the Adult Asthma Adherence Questionnaire™ (AAAQ) [41]. The AAAQ is a five-item questionnaire developed specifically as a screening diagnostic tool for adherence by care providers, as well as for identifying potential adherence barriers [42]. The first question is a general adherence monitoring question, and questions two to five determine specific barriers to adherence among individuals with low adherence (forgetting, no need, adverse effects, and costs). The AAAQ has been shown to have a high degree of construct validity and has proven to be a strong predictor of adherence, as measured through administrative health data [42]. There are alternative adherence questionnaires [43, 44], but they do not have the predictive power of the AAAQ [44], or consist of too many questions and thus are cumbersome to administer [43]. In addition, the AAAQ is particularly suited to the EmPhAsIS intervention given the separation of the adherence-monitoring question (question one) from those determining specific barriers to adherence (questions two to five). The transmission and receipt of text messages will be centralized and automated using the University of British Columbia (UBC) designed WelTel system. WelTel is an SMS support and engagement platform that will be administered at our research centre and accessed online by pharmacists through the study website. Centralizing text message transmissions minimizes the burden on pharmacists who will not have to send messages themselves, and reduces the delays and potential errors in the evaluation of responses.Follow-up of non-adherent individuals by community pharmacists: If the response to item one of AAAQ, received through SMS, is anything other than one (Agreeing completely), then this would indicate an adherence problem and the individual will be asked the rest of the adherence-barriers questions of the AAAQ (questions two to five) via SMS. Based on the responses, WelTel will generate an AAAQ adherence report that identifies potential adherence barrier(s) (such as cost or fear of side effects) to help facilitate and guide the pharmacist’s follow-up telephone call with the patient. A pharmacist will then follow-up with the individual within the next 24 hours. During the telephone follow-up, the pharmacist will administer the Asthma Control Test (ACT, a five-item validated and widely used questionnaire assessing asthma control) [41]. In separate training provided to pharmacists in the EmPhAsIS intervention group, webinars will provide step-by-step instruction on use of the WelTel platform as well as administration of the ACT over the telephone. Patient responses to the ACT items will be entered into a survey system that will automatically score the questionnaire in order to facilitate this step for the pharmacist. Based on the individual’s response to the ACT, the outcome of this phone interview may be counselling and education to address adherence problems, or a referral to the patient’s physician (if the individual receives a score of 19 or lower in the ACT, which may indicate the presence of uncontrolled asthma). For patients where the adherence problem is unintentional, the pharmacist will provide phone-based counselling and support, for example by clarifying instructions, offering suggestions on incorporating medication taking with the patient’s daily routine, and offering adherence tools such as calendars. For patients where the adherence problem is intentional, the pharmacist can provide education on the risks and benefits of treatment and non-treatment, evaluate adverse effects, and consider medication coverage options (or the use of alternative formulations). Figure 1 illustrates SMS transmission for pillars two and three of the EmPhAsIS intervention along with scenarios for instances of non-responses to the monthly SMS message. Pharmacists will log telephone calls, including response and non-responses, and in instances of non-responses, at least two follow-up attempts will be made.

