### Data collection and study follow-up

The design of the trial and the schematic of data collection and outcomes are illustrated in Figure 2. Pharmacists will screen for eligibility, obtain informed consent, and enroll patients at their pharmacy. Upon patient enrollment, pharmacists will securely fax the individual’s contact information to the study research coordinator. Prospective data will be collected by telephone interview by an interviewer at set time points as follows: 1) sociodemographic characteristics, such as age, education, income, BC provincial health number (baseline); 2) Asthma Control Test and Asthma Quality of Life Questionnaire (AQLQ) (baseline, 6 months, and 12 months); and 3) changes in the enrollment of the individual with the provincial healthcare system, changes in third-party insurance, as well as the frequency of receiving inhaler medications through samples. In addition to prospectively collected outcome data, we will also obtain data for our study sample through BC PharmaNet (http://www.health.gov.bc.ca/pharmacare/pharmanet/netindex.html) [45] and Population Data BC (http://www.popdata.bc.ca) [46] In brief, these are extensive data resources for applied health services research with data holdings spanning information on all dispensed medications, includes drug name (brand and generic), Canadian Drug Identity Code, date dispensed, quantity dispensed, days of supply (BC PharmaNet), outpatient services, hospital separations, and vital statistics (Population Data BC).

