#### Covariates

All the analyses will be adjusted for the following variables: age, sex, baseline level of asthma control, socioeconomic status (income and education), and coverage by any third-party insurance. We will also draw on administrative health records from the 12-month period before the study entry to measure other potential confounders such as comorbid conditions and general pattern of healthcare utilization (number of physician visits, hospitalization, and medication dispensations).

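### Randomizing pharmacies does not eliminate recruiter selection bias, because pharmacists who are not blinded to their arm still screen, consent and enrol the patients

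*Protocol article*

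**What the plan says.** Study design in the protocol article gives three reasons for using pharmacies as clusters. The first and third concern contamination within a pharmacy. The second is selection: if single pharmacists were randomized, the recruiter would also be the randomization unit, and the example given is "pharmacists randomized to the intervention group preferentially recruiting patients whom they know are at higher risk of medication non-adherence". The section concludes: "To eliminate such randomization problems, it was therefore pragmatically decided to randomize clusters at an organizational level".

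Other sections describe who recruits and what they know:

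- Data collection and study follow-up: "Pharmacists will screen for eligibility, obtain informed consent, and enroll patients at their pharmacy".
- Randomization: "It will not be possible for participating pharmacies to be blinded to which group they are assigned". The interviewer and the statistical analyst "will be blinded to group allocation".
- Pharmacies: besides separate webinars for each arm, pharmacists "will receive written study manuals specific to whether they have been assigned to the EmPhAsIS intervention or usual care group".
- Intervention group: "Patients attending pharmacies assigned to the intervention group will receive the EmPhAsIS intervention".
- Sample size calculation: the target is five patients in each of 74 pharmacies.

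The Covariates section fixes adjustment for age, sex, baseline asthma control, income, education and third-party insurance. It also plans to use health records from the year before entry to measure other possible confounders, among them the number of medication dispensations.

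**The concern.** The bias that the protocol describes needs two things: a recruiter who knows the arm, and some freedom over whom to approach. It does not need the recruiter to be the unit of randomization. Moving the unit from pharmacist to pharmacy therefore leaves both conditions in place.

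The freedom is considerable. Each pharmacy needs about five patients, drawn from new and existing ICS users over a 12-month recruitment period.

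The trait on which selection would act, likely adherence, is what the primary outcome measures. Neither intention-to-treat analysis nor the random pharmacy effect corrects this. The first keeps the randomized pharmacies in their arms, and the second allows for correlation within pharmacies. A systematic difference between the kinds of patient enrolled in the two arms passes into the estimated effect, and a larger sample does not shrink it.

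**Working it through.** **1. The three stated reasons against the described procedure**

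| Reason given | Does the pharmacy as unit address it? |
|---|---|
| Patient-level randomization: one pharmacist delivers both arms | Yes, each pharmacy delivers one arm |
| Pharmacist-level randomization: the recruiter knows the arm and may select | No, pharmacists who are not blinded still enrol |
| Shift work: overlapping care within a pharmacy | Yes, all staff of a pharmacy are in one arm |

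The two blinded roles act after enrolment. The article describes no independent or blinded recruiter, no consecutive enrolment, and no identification of patients before assignment.

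**2. The plan's own sample size**

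Inputs from Sample size calculation: a 10% improvement (taken here as 0.10 on the MPR scale), power 80%, ICC 0.06, five patients per pharmacy, N = 334. Statistical analysis gives two-sided 0.05. The article states no SD for MPR, so 334 cannot be confirmed directly and the SD has to be back-solved.

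- Design effect = 1 + (5 − 1) × 0.06 = 1.24.
- N = 4 × (1.96 + 0.8416)² × SD² × 1.24 / 0.10². Setting N = 334 gives SD = 0.293.
- The later steps agree with the article: 334/0.9 = 371, close to 370; 370/5 = 74; 74/2 = 37.

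**3. Standard error of the arm difference**

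SE = √(4 × 0.293² × 1.24 / 334) = 0.0357.

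**4. Effect of an assumed shift b**

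Let b be the amount by which arm-dependent recruitment moves the intervention arm's underlying mean MPR. The article gives no value. One way to picture it is b = share of recruits affected × their difference in MPR. If 20% are affected, a difference of 0.05 gives b = 0.01, and a difference of 0.25 gives b = 0.05.

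- Power for a true 0.10 effect, with the shift against the intervention: Φ((0.10 − b)/0.0357 − 1.96).
- Type I error with no true effect, shift in either direction: Φ(−1.96 + b/0.0357) + Φ(−1.96 − b/0.0357).

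| Assumed shift b | Power | Type I error |
|---|---|---|
| 0 | 80% | 5% |
| 0.01 | 71% | 5.9% |
| 0.02 | 61% | 8.7% |
| 0.03 | 50% | 13% |
| 0.05 | 29% | 29% |

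These figures assume that the covariates remove none of the shift. If adjustment removed half of a 0.05 shift (also an assumption), the remaining 0.025 would give about 56% power or 11% type I error.

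**The case against.** The strongest reply is that the plan already has partial protection. All analyses adjust for baseline asthma control and sociodemographic factors, and prior dispensing counts are to be drawn on. Posters, shelf-talkers, the website and social media bring some patients forward themselves. Most eligibility criteria are factual, both arms require a text-capable phone, and control patients also receive the education component. All of this stands, and it limits the likely size of the bias. It does not restore the claim. Pharmacists still control entry, a count of dispensations is not ICS possession, and adjustment cannot reach traits that are not measured, such as motivation.

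It is also fair to say that the order of events is inferred. The article never states that each pharmacy learns its arm before its first enrolment, and Figure 2 is not shown. Still, the lack of blinding, the arm-specific training and the reference to patients of already assigned pharmacies all point that way.

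Three stronger readings are tempting, and the document does not support them:

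- That patients consent knowing whether they will be texted. The article says only that written consent is obtained, not what patients are told about their arm.
- That pharmacies enrolling nobody would vanish from the analysis unnoticed. Nothing says they would go unreported, recruitment is to be monitored, and flow reporting is commonly left to the full protocol or the analysis plan.
- That the result will be biased in favour of the intervention. The protocol's own example, higher-risk patients in the intervention arm, would dilute the effect. A false positive needs selection in the opposite direction.

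**Conclusion.** The concern holds as a contradiction within the protocol article. Study design claims that a bias is eliminated, while the sections on pharmacies, randomization and data collection describe a procedure that leaves it in place. Randomizing pharmacies is a sound answer to contamination, and the choice of unit is not at fault.

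The size of the bias cannot be derived from the document. The power and type I error figures are illustrations that rest on an assumed shift, a back-solved SD of 0.293 and no covariate adjustment. At 0.01 the harm is modest. At 0.03, less than a third of the target effect, power is down to 50%. The figures show that the risk to the primary comparison deserves a prespecified response. They do not show that the trial will be biased by any given amount.

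**What to change.** 1. In Study design, withdraw the statement that pharmacy-level randomization eliminates recruiter selection bias. Say that it addresses contamination, and name selection by unblinded recruiters as a residual risk. State whether assignment is disclosed to a pharmacy before it enrols patients.
2. In Covariates and in the primary model, prespecify each patient's ICS MPR over the 12 months before enrolment, with a new-user indicator where there is no prior ICS supply. PharmaNet already provides dispensing dates and days of supply, and a 12-month look-back is already planned.
3. Compare baseline MPR by arm.

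The cost is slightly more analysis work on data that are already to be obtained. Selection on unmeasured traits remains, so the residual-risk statement is needed even with the adjustment.

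Optional, where feasible: identify or enrol a pharmacy's patients before its assignment is disclosed. This removes the mechanism for those patients, but it is a real trade-off. Texting could be delayed by weeks or months for the first patients enrolled. A cut-off would be needed for slow pharmacies, and follow-up would have to start from the same event in both arms.
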